   2. **Aims:** This prospective study aims (1) to design an image-based VR (IBVR) instruction for clinical medical education, (2) to compare HRV and CL in traditional video-based (VB) learning and novel IBVR-based learning, (3) to compare outcomes of mini-CEX, DOPS, and milestone between two modules, (4) to perform a qualitative evaluation of IBVR-based learning using a 360-degree video review, and (5) to assess various levels of novice learners (undergraduate medical students and postgraduate year residents) for their participation in and acceptance of this novel IBVR-based learning.
   3. **Study Designs:** This 3-year study includes two parts: (1) Design a VR-based curriculum including fundamental otolaryngological skills, and (2) Validation of an IBVR-based history taking and physical examination (H&P) learning activity using a blinded randomized, parallel-controlled trial in convenience-sampled novice undergraduate medical students and postgraduate year residents.
   4. **Materials and Methods:** This study will be implemented between August 1, 2017 and July 31, 2020. Firstly, a VR-based curriculum will be designed including H&P using the analysis, design, development, implementation, and evaluation model and a modified Delphi approach. VB module and IBVR module of the same contexts will be developed. Secondly, an IBVR-based H&P learning activity will be validated by measuring CL questionnaires, reaction time, HRV, mini-CEX, DOPS, milestones, global satisfaction scale and AttrakDiff2 questionnaires (n = 64). Age, sex, and cognitive style (determined by the Group Embedded Figures Test) of both groups are matched. Differences in variables of interests will be statistically analyzed.
2. **Study Design**
   1. **Study Type:** Interventional (Clinical Trial)
   2. **Actual Enrollment:** 64 participants
   3. **Allocation:** Randomized
   4. **Intervention Model:** Parallel Assignment
   5. **Intervention Model Description:** This randomized controlled trial will recruit 64 subjects who are novices in otolaryngology at an academic teaching hospital. The cognitive style of the participants is assessed using the Group Embedded Figures Test. The subjects are randomly assigned (1:1) to a novel image-based virtual reality group and conventional video-based group matched by age, sex, and cognitive style.
   6. **Masking:** Double (Investigator, Outcomes Assessor)
   7. **Masking Description:** Blinding to the purpose of the study during recruitment is maintained to minimize preparation bias. After randomization, the participants are unblinded and use image-based virtual reality model or conventional video-based model on a virtual reality eyeglass in an ordinary office environment for 10 minutes. Heart rate variation will be monitored during learning and cognitive load will be assessed by the participants. Subsequently, each participant will perform history taking and physical examination for a real patient in a teaching clinic. The competence will be evaluated using the mini-clinical evaluation exercise, direct observation of procedural skills (DOPS), and milestone assessments. Investigators and outcome assessors are blinded to their randomization and learning models.
   8. **Primary Purpose:** Health Services Research
   9. **Official Title:** A Study of Heart Rate Variability and Cognitive Load on Image-Based Virtual Reality Instructional Design in Otolaryngology
   10. **Actual Study Start Date:** April 24, 2018
   11. **Actual Primary Completion Date:** July 31, 2020
   12. **Actual Study Completion Date:** October 31, 2020
3. **Arms and Interventions**

| **Arm** | **Intervention/treatment** |
| --- | --- |
| *Experimental:* image-based virtual reality learning  The participants will undergo 10-minute image-based virtual reality learning for history taking and physical examination of otolaryngology. | *Other:* image-based virtual reality learning  The participants will use a whole-view, 360 degree image-based virtual reality to learn a competence of history taking and physical examination for otolaryngology and they can see the response of the staffs and standard patients (including image, voice, face expression, movement, ... etc). |
| *Active Comparator:* video-based learning  The participants will undergo 10-minute video-based learning for history taking and physical examination of otolaryngology. | *Other:* video-based learning  voice of the staffs and standard patients. |

1. **Outcome Measures**
   1. **Primary Outcome Measures:**
      1. Direct observation of procedural skills (DOPS) [Time Frame: DOPS will be assessed immediately after intervention.] Procedural skills of history taking and physical examination for otolaryngology will be evaluated using a DOPS assessment immediately after a 10-minute mini-clinical exercise. This assessment uses ten items (indication, explanation, preparation, sites, aseptic/safe procedure, completeness, request for help, recording, interpretation, and global assessment) with 10 (1-10) Likert scales (range: 10-100).
   2. **Secondary Outcome Measures:**
      1. Mini-clinical evaluation exercise (mini-CEX) [Time Frame: The mini-CEX will be assessed immediately after intervention.] Skills of history taking and physical examination for otolaryngology will be evaluated using a mini-CEX assessment immediately after a mini-clinical exercise. The Mini-CEX is a 10-minute direct observation assessment. This assessment uses seven items (interview, physical examination, professionalism, clinical diagnosis, explanation, efficiency, and global assessment) with 9 (1-9) Likert scales (range: 7-63).
      2. Milestones [Time Frame: The milestones will be assessed immediately after intervention.] Overall competence of history taking and physical examination for otolaryngology will be immediately evaluated using an assessment of milestones after a 10-minute mini-clinical exercise. This assessment uses five Likert-type levels (basic, focuses, appropriate, accurate, professional) (range: 1-5).
      3. Cognitive Load Scale (CLS) [Time Frame: The CLS will be assessed immediately after intervention.] Cognitive load of the specific intervention will be immediately evaluated using the Paas CLS questionnaire after an intervention. The Paas CLS questionnaire is a single-item measure of total cognitive load. Participants are asked to rate the perceived intensity of their mental effort with 9 Likert scales (1 = very, very low mental effort; 9 = very, very high mental effort).
      4. Task Load Index (TLX) [Time Frame: The TLX will be assessed immediately after intervention.] Task Load of the specific intervention will be evaluated using the National Aeronautics and Space Administration TLX questionnaire after an intervention. The questionnaire has six subscales: mental demand; physical demand; temporal demand; performance; effort, and frustration. Participants are asked to indicate the level of each dimension by making a mark on a visual analogue scale with a 21-point Likert scale (range: 0-20). Total cognitive load is interpreted as the sum of the six subscales (range: 0-120).
      5. Cognitive Load Component (CLC) [Time Frame: The CLC will be assessed immediately after intervention.] Component of cognitive load of the specific intervention will be immediately evaluated using the CLC questionnaire after an intervention. The CLC questionnaire has six subscales: difficulty, complexity, clarity, relevance, focus, and learning with 5 Likert scales (range: 6-30).
      6. Bidirectional feedback and reflection [Time Frame: The bidirectional feedback and reflection will be assessed immediately after intervention.] Bidirectional feedback and reflection will be immediate evaluated using a qualitative questionnaire after an intervention.
      7. Global Satisfaction Scale (GSS) [Time Frame: The GSS will be assessed immediately after intervention.] Global satisfaction of the specific intervention will be immediately evaluated using the GSS questionnaire with 11 Likert scales (range: 0-10) after an intervention.
      8. Pragmatic Quality (PQ) [Time Frame: The PQ will be assessed immediately after intervention.] PQ of the specific intervention will be immediately evaluated using the AttrakDiff2 questionnaire after an intervention. The AttrakDiff2 questionnaire contains 28 questions with 7 Likert-type scales. A PQ scale ranges from -3 to 3.
      9. Hedonic Stimulation (HQ-S) [Time Frame: The HQ-S will be assessed immediately after intervention.] HQ-S of the specific intervention will be immediately evaluated using the AttrakDiff2 questionnaire after an intervention. The AttrakDiff2 questionnaire contains 28 questions with 7 Likert-type scales. A HQ-S scale ranges from -3 to 3.
      10. Hedonic Identification (HQ-I) [Time Frame: The HQ-I will be assessed immediately after intervention.] HQ-I of the specific intervention will be immediately evaluated using the AttrakDiff2 questionnaire after an intervention. The AttrakDiff2 questionnaire contains 28 questions with 7 Likert-type scales. A HQ-I scale ranges from -3 to 3.
      11. Attractiveness (ATT) [Time Frame: The ATT will be assessed immediately after intervention.] ATT of the specific intervention will be immediately evaluated using the AttrakDiff2 questionnaire after an intervention. The AttrakDiff2 questionnaire contains 28 questions with 7 Likert-type scales. A ATT scale ranges from -3 to 3.
   3. **Other Outcome Measures:**
      1. Heart Rate Variation [Time Frame: At baseline for 2 minutes and during an intervention for 10 minutes.] Before and during an intervention, heart rate is continuously recorded. Heart rate variations will be calculated at baseline and during the specific intervention.
      2. Reaction time [Time Frame: At baseline, the 5th minute and the 10th time.] The dual-task paradigm with reaction time measurement is manually measured (seconds).
2. **Eligibility Criteria:**

| Ages Eligible for Study: | 20 Years to 65 Years   (Adult, Older Adult) |
| --- | --- |
| Sexes Eligible for Study: | All |
| Accepts Healthy Volunteers: | Yes |

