
- 1. **Cognitive Load Theory**

CL Theory is a conceptual framework relevant to activities that involve executing tasks, by focusing on the management of working memory during learning. In general, if the total CL in the learning situation results in a cognitive overload, i.e., the limits in working memory and information processing are exceeded, actual learning and skills acquisition can be impeded according to the CL theory. Theory of CL is one of the leading theories of learning and provides a theoretical framework of the cognitive architecture with the basic assumption that working memory and information processing is limited.^19^ The theory suggests 3 sources of CL in any learning situation: (1) the intrinsic load of the learning task, (2) the extraneous load provided by the learning situation, and (3) the germane load of the learning process itself.^20^ The intrinsic load is related to the task difficulty and the learner’s level of expertise. The extraneous load is related to how the task is presented and to elements that are unconnected to the goals of the task and not essential for learning. The germane load is related to the learner´s level of concentration, which is important to long-term storage of new information.^20^ Andersen *et al*. observed that the learners׳ CL in the learning situation in complex learning tasks such as learning the ear surgical procedure, should be considered because this could have implications for the organization of skills training.^21^ When the learner needs to integrate complex multisource information and psychomotor skills, learning tasks can impose an extraneous CL resulting in a cognitive overload. An efficient instructional design should aim to minimize extraneous load, to manage intrinsic load and to optimize germane load. Therefore, we can employ instructional strategies and design principles to lower the extraneous load and optimize intrinsic and germane loads, leading to more efficient learning.

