The use of simulation in health professional education has increased rapidly over the past 2 decades. VR simulation has predominantly been used to train health professionals and students for a variety of clinically related situations, especially in clinical training such as surgy^26^, endoscopy,^27^ general anesthesia,^28^ and emergency.^29^ Much desired outcomes in healthcare such as improvement of patient safety and the reduction in costs and morbidity after use of computer-enhanced training have been reported.^30^ Most of the previous studies and reviews concluded that “Because VR simulation is less complex it reduces the CL of the learner, in turn leading to better learning and making VR simulation training well suited for the initial training of novices.” However, the haptic interaction and different visual cues in VR simulation could impose additional CL compared with other training modalities. Accordingly, when we develop VR education, we should consider relevant differences in both the specific training modalities (i.e., virtual and cadaveric dissection training) and in the organization of clinical skills training in general.

Total CL has been measured with self-rating evaluation of learner’s mental effort, response time to secondary tasks, and psychophysiological measures.^20,31-35^ Instruments such as the Paas Cognitive Load Scale (CLS),^36^ the NASA Task Load Index (TLX),^37^ and the cognitive load component (CLC)^34^ have been used as measures of total cognitive load. In the dual-task paradigm, performance in a secondary-task estimates CL, e.g., by measuring reaction time in response to a visual, auditory, or tactile stimulus. Secondary-task reaction time performance has been demonstrated to detect changes in CL in surgical skills training of novices.^21,33^ However, testing predictions about the effects of different instructional design features requires sensitive and reliable measures of cognitive load. Without careful validation, the use of such measures in medical

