In the ***first-year study***, we will perform **needs assessments** of these fundamental otolaryngological skills in focused group (novice learners: 30 UME students, 20 PGY residents, and 10 junior otolaryngological residents), collection of **instructional materials** of H&P and **content validation** using the modified Delphi method in an expert panel (8 academic staffs and 2 department chiefs), **module establishment** of the VB and IBVR modules in first person view, and translate these to a **computer program**. **Outcome evaluation** using the mini-CEX for history taking, the DOPS for physical examination, the milestone assessment for level identification, the GSS questionnaire for satisfaction, and the AttrakDiff2 questionnaire for learning experience, and verify this VR-based learning tool in a **pilot study**. Meanwhile, we will measure their cognitive style using the GEFT test, CL using the CLS, the TLX, and CLC questionnaires, and the dual-task paradigm with reaction time measurement; measure HRV using a mobile HR measurement. The VB module and IBVR module consist of video and audio (non-haptic design). The main differences in these two modules the field of vision (VB: narrow view, 100-degree; IBVR; whole view, 360-degree) and involvement of staffs and patients (VB: voice; IBVR: image, voice, face expression, movement, response…, etc.). Their contexts were adjusted to the same levels by two senior investigators.

In the ***second-year study***, we will further collect instructional materials of ventilation tube insertion, preparation of navigation-assisted endoscopic sinus surgery, preparation of microscopic laryngeal surgery, and tracheostomy, and validate content, establish the VB and IBVR modules, translate these to a computer program, outcome evaluations, and verify this IBVR-based learning tool in a pilot study. We will measure their CL and measure HRV during the learning activity. We will improve our instructional design to reduce extraneous CL and increase germane CL using the CL theory and several PDCA-cycles.^57^

1. **Validation of an IBVR-based H&P learning activity using a blinded randomized, parallel-controlled trial in convenience-sampled novice UME and PGY learners**

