Three CL questionnaires are used in this study: the Paas CLS,^31^ the NASA TLX,^37^ and the Naismith CLC.^34^ The Paas CLS questionnaire is a single-item measure of total cognitive load. Participants are asked to rate the perceived intensity of their mental effort along a 9-point scale (1 = very, very low mental effort; 9 = very, very high mental effort). The NASA TLX has six subscales: mental demand; physical demand; temporal demand; performance; effort, and frustration.

Participants are asked to indicate the level of each dimension by making a mark on a visual analogue scale (range: 0–20). Total cognitive load is interpreted as the sum of the six subscales (maximum: 120 points). The Naismith CLC has six subscales to explore how different components of cognitive load relate to the Paas and TLX scales (range: 6–30). Two questions each are used to measure intrinsic, extraneous and germane load along 5-point Likert scales.

1. **Mini-CEX**

The American Board of Internal Medicine develop the mini-CEX for years. Mini-CEX is intended to facilitate formative assessment of core clinical skills. It can be used by faculty as a routine, seamless evaluation of trainees in any setting. The Mini-CEX is a 10-minute direct observation assessment or “snapshot” of a trainee-patient interaction. Faculty are encouraged to perform at least one per clinical rotation. To be most useful, faculty should provide timely and specific feedback to the trainee after each assessment of a trainee-patient encounter (range: 7–63).

1. **DOPS**

DOPS is developed by the Royal College of Physicians,^65^ and now forms part of workplace based assessments for doctors in the foundation year and those in specialist training including otolaryngology (range: 10–100). Most DOPS are completed by consultants, which is likely to be a reflection of the fact that otolaryngological trainees are well supported, with the majority of junior trainees having consultant supervision in theatre or within the theatre complex. A DOPS is specifically designed to assess procedural skills involving real patients in a single encounter. This is an important facet of DOPS which distinguishes it from other forms of assessment such as a supervisor's evaluation which relies on observation over a period of time. DOPS is a formative rather than summative tool and training for all those who are participating in DOPS assessments.

1. **Milestones:**

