Primary outcome is score of DOPS. Differences in scores of mini-CEX, DOPS, milestones, CLS, TLX, CLL, GSS, PQ, HQ-S, HQ-I, and ATT between IBVR module and VB module are compared using Mann-Whitney *U* test. Changes in reaction time and HRV between IBVR module and VB module are compared using Wilcoxon rank test. Percentage (%) of change ([intervention value – baseline value]/[baseline value] × 100) in reaction time as well as HRV will be calculated and compared with Mann-Whitney *U* test or Wilcoxon rank test as appropriate.

1. **Validation of basic IBVR-based surgical trainings using a randomized, controlled, crossover trial in convenience-sampled novice residents**

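### The CLC is given one 6-30 score and one between-arm test although it pools three kinds of load that should move differently, so a difference in the total has no single meaning.

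*Protocol*

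**What the plan says.** In the protocol's Secondary Outcome Measures, item 5 defines the CLC with one range: "The CLC questionnaire has six subscales: difficulty, complexity, clarity, relevance, focus, and learning with 5 Likert scales (range: 6-30". CL Measurements repeats that range, states the instrument's purpose ("The Naismith CLC has six subscales to explore how different components of cognitive load relate to the Paas and TLX scales") and describes its content: "Two questions each are used to measure intrinsic, extraneous and germane load along 5-point Likert scales".

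Cognitive Load Theory, in the introduction, gives the desired direction of each component: "An efficient instructional design should aim to minimize extraneous load, to manage intrinsic load and to optimize germane load". In the curriculum-design section, the paragraph on second-year module development sets the aim to "reduce extraneous CL and increase germane CL".

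The between-arm analysis of the history-taking and physical-examination trial, under Outcome Measurements and Statistics, covers "Differences in scores of mini-CEX, DOPS, milestones, CLS, TLX, CLL, GSS, PQ, HQ-S, HQ-I, and ATT between IBVR module and VB module" by Mann-Whitney U test. CLC is not in that list. CLL stands where it would be expected, and CLL is defined nowhere. The null hypothesis on cognitive load uses the same abbreviation. No between-arm comparison of the three components is written, and no scoring direction is given for any item.

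**The concern.** A sum is readable when its parts are expected to move the same way. By the protocol's own theory these parts are not: extraneous load is to be minimised, intrinsic load managed and germane load optimised. A single total lets a change in one component hide or imitate a change in another. A null result could mean no effect or two real effects that offset each other. A significant result could not be called good or bad without looking at the parts.

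The trial already has two measures of overall load, the Paas scale and the TLX total. What the CLC adds is the split into components, and the planned comparison gives that up.

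**Working it through.** **Inputs.** Six items on 5-point scales with range 6-30 (Secondary Outcome Measures, item 5). Two items per component (CL Measurements). 64 participants at 1:1, so 64 / 2 = 32 per arm. Two-sided 0.05 (Statistical Analysis). The shifts, SDs and correlations below are assumptions; the protocol gives none.

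**Step 1: the stated range.** 6 × 1 = 6 and 6 × 5 = 30, which reproduces 6-30. A mean of the items would run 1-5, and a two-item component 2 × 1 = 2 to 2 × 5 = 10. Only the unweighted six-item sum fits.

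**Step 2: which items form which pair.** The introduction links difficulty and complexity in the CLC to intrinsic load. Taking clarity and relevance as the extraneous pair, and focus and learning as the germane pair, is an inference from their order.

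**Step 3: direction, by arithmetic.** Let each item in an affected pair move 1 point.

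| Scoring | Module effect | Intrinsic pair | Extraneous pair | Germane pair | Total |
|---|---|---|---|---|---|
| A: higher = more load on every item | less extraneous, more germane | 0 | −2 | +2 | 0 |
| B: extraneous items scored positively (clearer = higher) | less extraneous, more germane | 0 | +2 | +2 | +4 |
| B | harder and less clear | +2 | −2 | 0 | 0 |

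Under A, the intended pattern disappears. Under B it shows, but a module that is both harder and less clear looks neutral, and a rise of 2 could mean more difficulty or more clarity.

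**Step 4: size.** Assume three independent components of equal SD, so the total has SD √3. For a standardised shift δ with 32 per arm, Mann-Whitney power is approximately Φ(δ × √(32/2) × √(3/π) − 1.96), where √(32/2) = 4 and √(3/π) = 0.977.

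- One subscore, δ = 0.6: 0.6 × 4 × 0.977 = 2.345; Φ(0.385) = 0.65. Simulated: 63%.
- Total, shifts −0.6 and +0.6: δ = 0, so the rejection rate is alpha. Simulated: 5%.
- Total, one component shifted by 0.6: δ = 0.6/√3 = 0.346; 1.354; Φ(−0.606) = 0.27. Simulated: 26%.
- Total, two components shifted by 0.6 the same way: δ = 1.2/√3 = 0.693; 2.708; Φ(0.748) = 0.77. Simulated: 75%.
- Total under scoring B, module harder and less clear by 0.6 SD each: δ = 0. Simulated: 5%.

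The simulations used 20,000 trials per case.

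**Step 5: 5-point items.** A second simulation used discrete items, a 0.75 SD shift per item and inter-item correlations from 0 to 0.6. Under scoring A the total rejected in 4.7-5.5% of trials, the extraneous score in 88-97% and the germane score in 87-97%. Under scoring B the total rose by about 2.8 points and rejected in at least 99%.

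**The case against.** The strongest reply is that the protocol never states item direction. A reader might infer that a module working as intended must show no difference on the CLC. The documents do not support that. It needs scoring A and shifts of similar size. If clarity and relevance are scored as named, the gains add, and the total is more sensitive than either subscore (about 75% against 63%). This stands, and it limits the point to interpretability.

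A further scoring, with difficulty and complexity reversed as well, would make every gain positive. Nothing in the protocol suggests it. The result would no longer measure load, and the theory section asks that intrinsic load be managed, not lowered.

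Other replies stand in part:

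- The word sum is written for the TLX and not for the CLC. The total is inferred from the 6-30 range and the single entry in the statistics, but no other score fits that range. AttrakDiff2, by contrast, is entered as four separate scores.
- The introduction says of the three questionnaires, the CLC included, that they "have been used as measures of total cognitive load". Even so, CL Measurements gives the CLC's purpose as exploring components. Spearman correlations are planned and could serve that purpose, so it would go too far to say the CLC cannot answer its question. They do not compare the arms.
- The aim of raising germane load belongs to module development in the second year, mainly for the surgical topics. It is not a hypothesis of this trial. The point therefore rests on the general principle in Cognitive Load Theory.
- Scoring rules are often left to a statistical analysis plan, so their absence alone is no finding. The single range and the single comparison are in the protocol itself.

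**Conclusion.** The point holds in this form: as defined, the CLC total pools three constructs and has no single interpretable direction under either plausible scoring. Steps 1 and 3 are arithmetic. The pairing of clarity with relevance, and of focus with learning, is inferred.

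The rejection rates show how far the answer depends on something the protocol does not fix. The same 0.6 SD effects give the total anything from about 5% to about 75%, while each shifted subscore stays near 63%. These figures rest on independent components of equal SD and on shifts chosen for illustration, and the 5% follows directly from making the shifts equal and opposite.

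The reach is limited to one of eleven secondary outcomes. The primary DOPS comparison and the sample size do not depend on it, and the Paas scale, TLX and reaction time also address load. The change should be made, but the trial's main conclusion does not turn on it.

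**What to change.** In Secondary Outcome Measures, item 5, and in CL Measurements, replace the 6-30 total as the between-arm outcome with three subscores: intrinsic, extraneous and germane load, each 2-10. State which two items form each subscore and whether a higher value means more or less of that load. Compare each subscore between arms and report the difference with a confidence interval.

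Replace CLL with these three scores in the null hypothesis on cognitive load and in Outcome Measurements and Statistics. The abbreviation recurs in the crossover part and should be reconciled there too.

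No new data are needed. The cost is three comparisons in place of one, which can be Holm-adjusted, and some loss of sensitivity if all effects run the same way (about 63% per subscore, before any adjustment, against about 75% for the total in the illustration).
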